### Statistical analysis

A dataset will be prepared including the information from all patients using the Redcap platform. Statistical analysis will be performed using Stata statistical software (version 13.0). The data analysis will comprise the estimation of the mean (standard deviations) for continuous and absolute frequency (percentages) for categorical variables. The effect of the home-based exercise program on the continuous variables over the intervention period will be determined using a linear mixed model. For categorical variables, generalized estimated equations with log link and binomial distribution will be performed to evaluate changes in the proportion of individuals between groups over the time. All measures performed in the intervention and control group will be used, regardless of losses to follow-up or compliance to the protocol during the intervention period, characterizing an intention-to-treat analysis. The variable of interest will be the interaction between time × treatment, which estimates the change rate of the outcome over time. Protocol analysis including only completers will also be performed. Adjustments for baseline prognostic variables will be made in case of unbalance distributions between the groups. A *p*-value < 0.05 will be considered significant for all statistical tests.

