### Sample size

The sample size was calculated based on the findings by Carta et al. (73), which evaluated the effect of a physical exercise program on the QoL. In this study, there was a difference of 2.2 (± 2.1) points for the intervention group and 0.0 (± 3.2) point for the control group in the physical domain of the WHOQOL-Bref questionnaire (46). Assuming α = 0.05 and β = 0.10 and inflating the sample by 20% for eventual losses to follow-up, a total of 80 individuals will be necessary to perform the present study (40 in each group).

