### Interim analysis and stopping rules

Two interim analyses are planned. The first will be conducted when the 40th participant completes 3 months of follow-up and the second when the last recruited participant completes 3 months of follow-up. Trial interruption for ethical reasons due to either positive or negative results exceeding expectations may be recommended by an independent committee. The prespecified stopping rules are >100% difference between group in any outcome, serious adverse events twice as frequent in one of the groups including death, Chagas cardiomyopathy progression, acute myocardial infarction, unstable angina, cardiac arrest, incident HF, and stroke. All these estimates should have a significance level <0.01 in any of the interim analyses.

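### Two interim looks may stop the trial on a positive result at p<0.01, yet the final test keeps the full 0.05; if a crossing is acted on, the stated α is modestly exceeded

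*Protocol article*

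**What the plan says.** Three sections of the protocol article bear on the error rate of the primary comparison.

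- *Sample size* plans with "Assuming α = 0.05 and β = 0.10", based on the physical domain of the WHOQOL-Bref, and arrives at 80 participants.
- *Interim analysis and stopping rules* plans two looks: when the 40th participant, and then the last recruited participant, completes 3 months. It says: "Trial interruption for ethical reasons due to either positive or negative results exceeding expectations may be recommended" by an independent committee. The outcome rule is a between-group difference above 100% in any outcome. A separate rule concerns serious adverse events. Of these rules the section adds: "All these estimates should have a significance level <0.01 in any of the interim analyses".
- *Statistical analysis* closes by stating that a p-value below 0.05 "will be considered significant for all statistical tests".

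The article gives no reduced final level, no alpha-spending function and no statement that the looks are for safety only.

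**The concern.** Read together, these sections give the primary comparison up to three occasions for a positive conclusion, at nominal levels 0.01, 0.01 and 0.05. The last occasion alone uses the whole planned 0.05, so whatever the looks add comes on top.

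This is not a detail left for a later document. Both the interim and the final level are stated, and they do not fit the stated overall α. At stake is the error rate of the main claim in a trial described as a phase 3 superiority trial. If the looks can stop for benefit, a final p-value just under 0.05 would be called significant without meeting an overall 5% level. Narrowing the stopping rule to one quality-of-life score would not remove the problem, because the levels would still be 0.01, 0.01 and 0.05.

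**Working it through.** **1. Reproduce the planned size.** Inputs from *Sample size*: "there was a difference of 2.2 (± 2.1) points for the intervention group and 0.0 (± 3.2) point for the control group", α = 0.05, power 0.90, 20% losses.

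- Pooled SD = √((2.1² + 3.2²)/2) = 2.706.
- n per arm = 2 × (2.706 × (1.960 + 1.282)/2.2)² = 31.8, rounded up to 32.
- 32/0.80 = 40 per arm, 80 in total, as stated.
- A one-sided 0.05 gives 26 per arm, 33 after losses, 66 in total, which does not match.

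The planned size therefore spends the full two-sided 0.05 on one final test.

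**2. Overall error with the two looks.** Let Z1 be the statistic at look 1 (40 participants, 3 months), Z2 at look 2 (80 participants, 3 months) and Z3 at the end (6 months). Under the null they are taken as jointly normal with

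- corr(Z1, Z2) = √(40/80) = 0.707,
- corr(Z2, Z3) = ρ,
- corr(Z1, Z3) = 0.707ρ.

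Here ρ is the correlation between 3-month and 6-month results. The article does not give it, so it is an assumption, shown from 0.5 to 0.9. The critical values are 2.576 (p<0.01) and 1.960 (p<0.05). The more than 100% condition is left out at this step. Simulation with 3 million draws gives:

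| ρ | Either-direction stops: P(\|Z1\|>2.576 or \|Z2\|>2.576 or \|Z3\|>1.960) | Favourable stops only: P(Z1>2.576 or Z2>2.576 or \|Z3\|>1.960) | False claim of benefit: P(Z1>2.576 or Z2>2.576 or Z3>1.960) |
|---|---|---|---|
| 0.5 | 0.064 | 0.057 | 0.032 |
| 0.7 | 0.061 | 0.056 | 0.031 |
| 0.9 | 0.056 | 0.053 | 0.028 |

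The reference value is 0.05 for the first two columns and 0.025 for the last. The additive ceiling for the first column is 0.01 + 0.01 + 0.05 = 0.07. The two looks alone spend about 0.018 when both directions count.

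**3. Add the more than 100% condition.**

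- *Read on changes*, as the absolute difference in change exceeding the absolute control change. With a common mean change of 0 to 2 points and ρ from 0.5 to 0.9, the either-direction error is 0.064 to 0.053. The condition blocks few crossings.
- *Read on raw scores*. *Quality of life* scores each domain from 1 to 5, so a difference above 100% needs, for example, a mean of 2.0 against one above 4.0. This is practically unattainable, and the primary outcome then adds almost nothing to the 0.05.

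**4. Final level that restores 0.05 if the looks stay at p<0.01.** It is about 0.043 (ρ = 0.5) to 0.047 (ρ = 0.9) for favourable stops only, and about 0.035 to 0.043 for both directions.

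**5. Power at the reduced level.** With 32 evaluable per arm, power = Φ(2.2/(2.706 × √(2/32)) − z) = Φ(3.25 − z), where z is the two-sided critical value.

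| Final level | Power |
|---|---|
| 0.05 | 90.2% |
| 0.045 | 89.4% |
| 0.04 | 88.4% |
| 0.035 | 87.4% |

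**The case against.** A reader might infer that the stated α is exceeded outright. The article does not support that, for four reasons.

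- *The rule has two parts.* It needs the more than 100% difference as well as p<0.01, and the scale of the percentage is not defined. On raw scores the excess vanishes. The change-score reading is borrowed from how *Sample size* expresses the effect; the stopping section does not state it. This stands and makes the finding conditional. It does not remove the finding, since a stated error rate should not hang on an unstated scale.
- *Stopping is discretionary.* A committee may recommend it on ethical grounds, and nothing says that a crossing is itself a claim of benefit. This also stands: the figures apply only if a crossing is acted on as a positive result.
- *The larger figures count crossings in the harm direction.* One might say that the three chances of declaring benefit sum to more than 0.05. They do not: that chance is 0.028 to 0.032, against 0.025. For a positive stop the relevant two-sided figure is 0.053 to 0.057.
- *The looks may hold more than 3-month data.* As an illustration, assume even recruitment over 18 of the 24 months in *Results*. At the second look about 80 × 15/18 ≈ 67 participants would then have 6-month values. If all accrued data are used, overall α is about 0.055 to 0.057, or 0.052 to 0.053 for favourable stops only. The excess shrinks but remains.

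It can also be said that alpha allocation belongs in an analysis plan or committee charter. That would answer a silent article. This one applies 0.05 to every test, so a later document that controlled α by lowering the final level would have to contradict it.

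**Conclusion.** The concern holds in conditional form. If a crossing is acted on as a positive result, and the more than 100% condition is read on changes, the levels 0.01, 0.01 and 0.05 do not keep the planned 0.05.

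The excess is modest. It is about 0.3 to 0.7 percentage points when only favourable crossings stop the trial (0.053 to 0.057), and about 0.6 to 1.4 when both directions count (0.056 to 0.064). These ranges leave the more than 100% condition out and rest on looks at 3-month data and an assumed correlation of 0.5 to 0.9. If the condition is read on raw 1-5 scores, or if the looks never lead to a claim of benefit, the final 0.05 is sound. The article does not say which of these applies, and that is what needs settling.

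**What to change.** Before the first look, name one primary quality-of-life comparison and adopt one of the following.

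- **No stopping for benefit.** State that the looks cannot stop the trial for benefit or support a claim of it. The final 0.05 then stands, at no cost in power.
- **A much stricter interim level.** For example p<0.001 at both looks. With the final level left at 0.05 the overall α is 0.0504 to 0.0512 (both directions, ρ 0.9 to 0.5). That is still a shade too high, so set the final level from a stated group-sequential or alpha-spending boundary, at or marginally below 0.05. The cost in power is negligible.
- **Keep p<0.01 at the looks and lower the final level.** Use about 0.043 to 0.047 if only favourable crossings can stop the trial, or 0.035 to 0.043 if both directions count. Say which applies, and fix the value from a stated boundary. Planned power falls from about 90% to roughly 87-89% with 32 evaluable per arm. At final levels of 0.045 to 0.035, holding 90% would need 33 to 35 evaluable per arm, or 42 to 44 after 20% losses (84 to 88 in total).

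Under the second or third option, amend the closing sentence of *Statistical analysis* so that its 0.05 no longer governs the final primary test. If stopping for benefit is kept, also define the scale of the more than 100% difference. The change is a sentence or two of text, and the first two options need no extra participants.

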### Ethical aspects

The present research was approved by the Institutional Review Board of the Evandro Chagas National Institute of Infectious Disease (approved on March 19, 2021 under number 4.629.748). The researchers involved in the present work are committed to maintain the confidentiality and privacy of the data obtained. The results obtained in this work will be published in scientific communications, maintaining the anonymity of the participants. There are no conflicts of interest involved in this work on the part of the researcher or collaborators, nor any restriction regarding the public disclosure of the results, which will occur whether they are favorable or not to the researcher’s hypothesis.

To be included, all patients must sign an informed consent form that will follow the good clinical practice standards. Patients will be instructed to read (or listen, in cases where the patient has difficulty reading) the consent form, without time restrictions, and will receive explanations for any doubts regarding the objectives and procedures to be adopted during the procedure. All participants will be informed that participation is voluntary, and that refusal to participate will not result in any harm to their treatment in the institution. They will be also advised that they can withdraw from participating in the study at any time.

At the end of the study, participation in the exercise program will be offered to individuals allocated to the control group if the results indicate an important effect of exercise in improving the investigated parameters.

## Results

The planned flow diagram is presented in Figure 2. The trial recruitment is planned to start in January 2023, and data collection is expected to be concluded in December 2024. The trial findings will be presented in accordance with the CONSORT (Consolidated Standards of Reporting Trials) reporting guidelines. No results are available as of manuscript preparation.

**FIGURE 2 F2:**
[figure not shown]
Planned flow diagram of the study.

## Discussion

Previous studies demonstrated that individuals with the indeterminate form of CD, despite its good prognosis, already have some subclinical abnormalities in comparison to non-infected individuals. CD is a neglected disease associated with low socioeconomic levels that may negatively impact on several aspects of mental health and QoL. In addition, due to the change in the epidemiological profile of CD population, many individuals have changed their lifestyles, with greater intake of inappropriate foods, decreased physical activity levels, greater exposure to stress and worsening of sleep quality, which in turn are associated with a higher incidence of numerous chronic diseases. Taken together, such changes can negatively impact the prognosis of these patients and decrease their QoL (74–76).

In this sense, regular physical exercise has been proposed as an important intervention strategy in the treatment of numerous chronic diseases, in addition to contributing to the improvement of several parameters of the physical and mental health (77, 78). However, studies evaluating the effects of a physical exercise program in individuals with the indeterminate form of CD were not found in the literature. Thus, it is urgently needed to evaluate the effects of a physical exercise program in individuals with the indeterminate form of CD. From the knowledge generated by the present study, public health intervention strategies aiming to improve physical and mental health parameters may be implemented more effectively in this population.

## Ethics statement

The studies involving human participants were reviewed and approved by the Evandro Chagas National Institute of Infectious Disease Ethics Commitee. The patients/participants provided their written informed consent to participate in this study.
